## Abstract

**Background:**

The global epidemic of type 2 diabetes (T2D) and obesity has been translated into pregnancy, with approximately 18% of women being diagnosed worldwide with Gestational Diabetes Mellitus (GDM). Whilst preventive strategies have proven effective in the non-pregnant context, attrition rates are high and there is an urgent need to develop a customized, pragmatic lifestyle intervention for women both during and after pregnancy. Diet and exercise modification, behavioral support, and Commercial Weight Management Organizations have been strongly recommended to aid postpartum weight reduction for mothers with previous GDM, subsequently reducing their risk of developing obesity and T2D. This study, informed by a previous pilot study, aims to determine the effectiveness of a pragmatic pregnancy and postpartum lifestyle modification program for overweight women with previous GDM (PAIGE2) to reduce body weight at 12 months postpartum.

**Methods/design:**

This paper summarizes the protocol for the PAIGE2 study, which has been developed based on results from a pilot study (PAIGE). A six center, two parallel arm, 12-month, randomized controlled trial will be conducted across Northern Ireland and the Republic of Ireland (3 centers each), involving 340 women with GDM and body mass index ≥25 kg/m^2^ recruited during pregnancy. The lifestyle intervention involves a one-hour virtual educational program (to take place at 32-36 weeks gestation). Postpartum, the intervention will include monthly phone calls, weekly motivational text messages, weekly step counts, and referral for three months to a Commercial Weight Management Organization (Slimming World). The control arm will receive usual care as offered by the local maternity hospital. The primary outcome is weight loss at 12 months postpartum. Study visits for anthropometric and clinical measurements, fasting blood samples, questionnaires pertaining to health, wellbeing and physical activity will take place at 6 weeks, 6- and 12-months postpartum. Focus groups will be conducted with intervention mothers’ post-intervention to determine the acceptability of the study design including utility of a Commercial Weight Management Organization, feasibility of remote patient contact, family involvement and patient satisfaction.

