#### Pilot study

3.1.1

The study has been designed and developed based on results of a recently completed pilot RCT (PAIGE) (52). The study, which was informed by focus groups, clearly highlighted the demands on these women and the key issues to consider in future lifestyle interventions, including the need for simplicity, to involve partners/and or families, to consider supportive care and be open to partnership between CWMOs and NHS. The PAIGE2 study, whilst having similar overall objectives to PAIGE, has been specifically modified to reflect the information gained from PAIGE participants and in particular the challenges of the women in the postnatal period. As part of the initial PAIGE pilot, study focus groups were carried out with participants who completed the study. As a direct consequence of this feedback, PAIGE2 has been designed to make it easy for women to take part and to remain in the study, with recruitment now taking place during pregnancy at routine review clinics rather than at 6–8-week follow-up visit, which was challenging for women to attend and had high attrition rates.

The PAIGE2 research proposal has been reviewed by women with GDM during a recent pregnancy prior to submission thus ensuring that researchers complete the circle of patient involvement in the proposal. In addition, service users and the public will be closely involved in the study and women with a history of GDM will be invited to sit on the Project Board. The involvement of users within the research process will be an important guide to local researchers in finalizing wording for patient information sheets, local recruitment strategies and in relation to supporting women while on the intervention.

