#### Sample size

3.1.7

Assuming the same variability in weight loss as was observed in the pilot study (52) (standard deviations of 7.0 and 3.9 kg in the intervention and control groups, respectively) and a 40% drop out rate (including women diagnosed with overt diabetes on the basis of a fasting glucose sample postnatal), it is estimated that a trial of 340 women should yield 200 evaluable subjects (100 in each of the intervention and control groups) which will be sufficient to detect a 3kg difference in maternal weight at 12 months after delivery with >90% power at the 5% level of significance.

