#### Control group

3.2.2

Women in the control arm will receive routine antenatal care as offered by their individual maternity hospital. When the study is concluded, the control group will be offered referral to Slimming World (12 consecutive weeks) free of charge and will be given access to the educational resources from the one-hour educational session.

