##### Timepoint one

3.2.3.1

Timepoint one will be the first study contact and will take place over the phone before 32-36 weeks gestation. Informed consent will be obtained at this point, followed by collection of baseline clinical and demographic data and questionnaire completion. Relevant clinical and obstetric data will be abstracted from patient notes and recorded in study specific case report forms.

Those women randomized to the lifestyle intervention will be enrolled into the study in small groups where they will receive an educational program lasting around one hour (as described above). They will also be given an activity tracking device (Fitbit) to allow them to become familiar with this technology during pregnancy. This device will either be posted to participating women or collected from research staff at the women’s next antenatal appointment. The education program will be led by a PAIGE2 research nurse or dietitian trained in motivational interviewing and will cover topics including GDM as a risk factor for future disease, healthy eating, physical activity, fitness tracker use, methods to reduce the risk of diabetes in subsequent pregnancies in the longer term, and ideas for maximizing peer support. The program will be loosely based on that used in the DPP (53) and designed to augment rather than duplicate the information the women will receive from Slimming World.

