Subsequent contact with the women will be by text or telephone a call. The frequency of contact by text message will be weekly for the initial month (to persuade the women to sign up for the CWMO) and then fortnightly for the remainder on the study. Structured telephone calls will occur monthly, and include information of physical activity, barriers to achieving their diet and physical activity goals, as well as suggested solutions. Participants who are successful during the first three-month period of enrolment with Slimming World (gauged by attending at least 9 out of 12 sessions or demonstrated weight loss), will be offered a second funded three-month membership to maximize any benefits obtained during the program. After the second free three-month Slimming World program, women will be able to continue to attend Slimming World for the rest of the study if they desire, at their own discretion. Partners of the women in the intervention arm will also be invited to participate in the trial. Partners consent will be obtained either by post or in person at the same 6-8 post gestational timepoint, and they will subsequently be offered a fitness tracking device like that of their partner. Intermittent contact *via* text will be made with the partner to feedback on their physical activity.

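### After 6–8 weeks the intervention arm has about 35 further contacts and a voucher, while the referral promised to control women is not tied to their 12-month weight; with 40% planned loss, follow-up could differ by arm

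*Protocol article*

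**What the plan says.** **Intervention arm after delivery.** The Abstract (Methods/design) states: "Postpartum, the intervention will include monthly phone calls, weekly motivational text messages, weekly step counts". Section 3.2.3.2 gives a different text frequency: "weekly for the initial month (to persuade the women to sign up for the CWMO) and then fortnightly for the remainder on the study". It adds that "Structured telephone calls will occur monthly". A 12-week Slimming World voucher is offered at the 6–8 week contact, with a second funded membership for women who succeed in the first. The activity tracker is issued earlier, at timepoint one in pregnancy (3.2.3.1).

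**Control arm.** "The control arm will receive usual care as offered by the local maternity hospital" (Abstract). Section 3.2.2 adds: "When the study is concluded, the control group will be offered referral to Slimming World (12 consecutive weeks) free of charge", together with access to the educational materials.

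**Both arms.** Data contacts follow at 6 and 12 months, and a woman may send a home weight instead of attending (3.2.3.3).

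**Loss and analysis.** Section 3.1.7 allows for 40% dropout, including women found to have overt diabetes, and expects "200 evaluable subjects (100 in each of the intervention and control groups". Section 3.1.1 says of the pilot's 6–8 week visit that it was one "which was challenging for women to attend and had high attrition rates". Section 3.1.4 says that the trial cannot be blinded, and has the statistician regularly review the numbers randomized to each arm. Section 3.3.1 plans analysis of covariance, a complete-case analysis of key outcomes, and multiple imputation as a sensitivity analysis.

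**The concern.** In this article, everything that keeps a woman in touch with the trial between 6–8 weeks and 12 months, apart from data collection, belongs to the intervention. That is legitimate as a treatment contrast, but it may also act as a retention device in one arm only. Control women know their allocation, and what they are promised does not depend on giving a 12-month weight.

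If the women lost differ in weight change from the women retained, and do so to a different extent in the two arms, the women weighed at 12 months no longer form randomized groups. Imputation as usually run assumes that missingness depends only on recorded data, so it lessens this risk without removing it. The one by-arm check that the article states counts women randomized, not weights obtained, and would not show the problem as it developed.

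**Working it through.** **1. The plan's own figure.** Inputs from 3.1.7: 340 women, 40% loss, SDs of 7.0 and 3.9 kg, difference 3 kg, 5% level (taken as two-sided).
- Evaluable: 340 × 0.60 = 204, stated as 200.
- SE at 100 per arm: √(7.0²/100 + 3.9²/100) = √0.6421 = 0.801 kg.
- Power (normal approximation): Φ(3/0.801 − 1.96) = 96.3%. This agrees with the stated figure of more than 90%.

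**2. Contacts from week 6–8 to week 52** (44–46 weeks).
- Texts by 3.2.3.2: 4 weekly + (40 to 42)/2 fortnightly = 24–25.
- Monthly calls: 44/4.345 to 46/4.345 = 10.1–10.6, so 10–11.
- Total: about 34–36.
- On the Abstract's weekly texts: 44–46 texts plus the calls, about 54–57.
- Control contacts described in the article: the two data contacts, which the intervention arm also has.

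**3. Illustration of a shift in the estimate.** The loss splits and the gap are assumptions; the documents give neither. Let d be the amount by which retained women lose more weight than lost women, after adjustment, and take d equal in both arms. Mean loss is held at 40% of 170 per arm.

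Shift against the intervention = (control loss − intervention loss) × d.
Power = Φ((3 − shift)/SE − 1.96).

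| Loss, intervention/control | Evaluable | SE (kg) | Shift, d = 2 to 4 kg | Power for 3 kg |
|---|---|---|---|---|
| 40%/40% | 102/102 | 0.793 | 0 | 96.6% |
| 35%/45% | 110.5/93.5 | 0.779 | 0.2–0.4 kg | about 95–92% |
| 30%/50% | 119/85 | 0.769 | 0.4–0.8 kg | about 92–82% |

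At 30%/50% the shift is 0.4/3 to 0.8/3, or 13–27% of the 3 kg target.

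**4. Equal loss with unequal gaps.** If loss is 40% in both arms, with d = 3 kg in the intervention arm and 0 in the control arm, the shift is 0.40 × 3 = 1.2 kg in favour of the intervention. The zero in the first row of the table therefore depends on assuming the same d in both arms.

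**The case against.** The contact imbalance is the treatment under test against usual care; it is not an error. The article condenses a fuller protocol, and reminder schedules and contact attempts are commonly left there. That the article describes no retention contact for control women does not show that none exists. This stands, and it is why the reminder part of the fix is conditional.

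A reader might infer that loss will probably be higher in the control arm and will dilute the effect. The documents do not support that. They give no loss by arm. The pilot's 6-month comparison had 31 and 29 women, which points to no imbalance, although without the numbers randomized it does not show equal retention either. The high attrition in 3.1.1 concerns the pilot's 6–8 week visit, and PAIGE2 responded by recruiting in pregnancy. Part of the 40% is exclusion for overt diabetes, or women who never attend after delivery (3.1.4), and later contact cannot drive these losses. If, as an assumption, 20 points were lost by 6–8 weeks in each arm, a 30%/50% split would need 10 against 30 points of later loss, a threefold difference.

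There are also mitigations. Either arm may send a home weight, control women are promised a free referral, baseline and center are adjusted for, and imputation is planned. The wording on the referral does not say whether it means the woman's own last contact or the end of the trial. What remains is that on either reading the offer is not linked to recording her 12-month weight.

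**Conclusion.** The point holds as a risk to follow-up, not as a demonstrated bias. The contact imbalance is documented: about 35 contacts on the 3.2.3.2 schedule, against none described for control women beyond the shared data contacts. The 40% planned loss, the lack of blinding and the untied control offer are also documented. That loss will be unequal, or that any bias will run in a particular direction, is not.

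The sizes in the working rest wholly on assumed splits and gaps. The milder split leaves power above the stated 90%; the larger one can take it below. Equal loss would not by itself remove bias, so the aim is low loss as well as balanced loss. The severity is optional: a cheap improvement to a stated rule. Separately, the two statements of text frequency contradict each other and must be reconciled.

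**What to change.** 1. In 3.2.2, replace the offer at the conclusion of the study with an offer of the promised referral and materials to each control woman at her own 12-month contact, after her weight is recorded.
2. Unless the full protocol already does so, specify one follow-up procedure for both arms, separate from the motivational contact. It would use the same content-neutral reminders (including the home-weight option), at the same times before the 6- and 12-month contacts, with the same number of attempts.
3. In 3.1.4, have the statistician's existing review also count weights obtained by arm. This shows unequal loss but cannot detect informative loss that is equal in number.
4. Reconcile the text frequency in the Abstract with that in 3.2.3.2.

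The cost is a short amendment and a few messages per woman. The referral is already promised, so only its timing changes, and no extra staff, visits or participants are needed. The small downside is that control women receive a few neutral messages beyond usual care.

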**Discussion:**

The PAIGE2 study will address the gaps in previously conducted research and, if positive, has the potential to have major public health implications for the prevention of future GDM and subsequent T2D.

**Clinical trial registration:**

https://clinicaltrials.gov/ct2/show/NCT04579016?term=NCT04579016&draw=2&rank=1, identifier NCT04579016.

## Introduction

1

Gestational diabetes mellitus (GDM), classified as glucose intolerance with first recognition or onset during pregnancy, is a global health problem with reported prevalence rates of 2-18% (1, 2). A major compounding factor is excessive maternal weight and current estimates suggest that 50% of women of childbearing age are either overweight or obese (3). Women with GDM have a greater than 50% risk of developing GDM again in a future pregnancy and a 7-fold increased risk of type 2 diabetes (T2D) compared to women without GDM (4). Being overweight during pregnancy can significantly increase the risk of miscarriage, GDM, pre-eclampsia, macrosomia, instrumental delivery or caesarean section (3). Excessive gestational weight gain and postpartum weight retention are also recognized risk factors for chronic obesity (5). At 6-18 months postpartum, between 15 to 20% of women have retained a minimum of 5 kg body weight compared with pre-pregnancy body weight (6). GDM risk factors are comparable to those of T2D and the metabolic syndrome, and in the long-term, weight management may reduce T2D risk, obesity, coronary heart disease and some cancers (7).

In addition to the maternal health implications of GDM and obesity, babies born to mothers with GDM display increased rates of macrosomia, congenital malformations, admission to intensive care and fetal death (8, 9). In the longer term, these children are at greater risk of subsequent obesity and T2D (10–13). Most recently, a 10 year follow up of 4747 mother-offspring dyads from the Hyperglycemia and Adverse Pregnancy Outcome Study showed that GDM was associated with 2-3-fold higher rates of obesity in the offspring, controlled for confounding factors, with major implications for future generations (14). In a study by Catalano and colleagues, maternal pre-gravid body mass index (BMI) was the greatest predictor of childhood obesity, “independent of maternal glucose status or weight” (15).

Lifestyle modification can inhibit or impede the development of T2D in high risk non-pregnant persons (16), whereby a meta-analysis reported a relative risk of T2D development of 0.55 (0.44-0.69) with modest weight loss (17). Nutrition and physical activity collectively appear to be more successful than nutrition only in promoting weight loss post-delivery (18), and the addition of individual or group counselling in combination with written and telephone contact or diet and exercise diaries may be beneficial (19). An appraisal commissioned by the UK National Institute for Health and Care Excellence (NICE) determined that studies after childbirth are urgently required on the cost-effectiveness of weight management interventions and whether it is possible to prevent T2D (20, 21). Additionally, no consensus has been reached as to the individual constituents of the ‘optimal’ postpartum intervention, with many queries regarding the role of diet versus physical exercise, group versus individualized therapy, and the use of internet technology remaining unanswered (22–26).

In the Diabetes Prevention Program (DPP) 10-year follow up, it was reported that although women with a history of GDM experienced less weight loss compared with the general DPP population, they experienced a 35% decrease in T2D development as a result of an intensive lifestyle intervention (27). However, other papers have indicated poor diet quality and low physical activity levels amongst women with previous GDM (28–31). A recent systematic review (32) identified 10 randomized controlled trials (RCTs) of postnatal behavioral interventions in women with previous GDM. Only four RCTs found a significant result for body weight or BMI (33–36). None of those four RCTs showed a significant decrease in T2D incidence, however the pooled incidence on meta-analysis was significant (-5.02 per 100; 95% CI -9.24; -0.80). Most interventions addressed both nutrition/diet and physical activity (29, 30, 33–35, 37–39); one focused solely on physical activity with no effect on insulin resistance or body weight (40) and one exclusively addressed diet (36), finding an effect on body weight and 2-hour glucose but a non-significant reduction for fasting glucose. In summary, the authors stated that they were not able to suggest a particular intervention for T2D prevention in women with previous GDM.

There is increasing evidence that step count-based programs are successful in instigating increased ambulatory activity both among the general public and those with T2D for up to 6 months (41). On the other hand, the literature would suggest that the responsiveness of adults to simply wearing a pedometer is minimal and likely short-term (42, 43), indicating that additional support is needed to enable sustainable behavior change.

The Gestational Diabetes’ Effects on Moms cluster RCT (44) showed that a DPP-derived lifestyle intervention moderately “reduced postpartum weight retention and improved physical activity in women with a recent history of GDM” (44). These women had telephone sessions between 6-24 weeks postpartum and were urged to set weekly physical activity and nutrition goals. The primary outcomes involved reaching pre-gravid weight (if pre-gravid BMI < 25.0 kg/m^2^) or losing 5% of pre-gravid weight (if BMI ≥ 25.0 kg/m^2^). Overall, “significantly more women in the intervention group met the weight loss goal and displayed larger increases in physical activity levels compared with the usual care group” (44).

Recently published Department of Health, Health Technology Assessments Position Statements and UK NICE guidelines (20, 21), have highlighted the growing problem of pregnancy-associated weight gain, with its relevance to GDM, as a major area for urgent future public health research. This issue was further highlighted by the Hyperglycemia and Pregnancy Outcome study which estimated the prevalence of GDM in Belfast, using the new International Associations for Diabetes in Pregnancy Study Groups (IADPSG) diagnostic criteria is 15.5% (45). Although there is controversy surrounding the different methods to diagnose GDM, the IADPSG criteria have been widely accepted for more than a decade and are endorsed by the World Health Organization (46). The UK National Institute for Clinical Excellence, in their Obesity Guidance (2006) (47), highlighted the importance of providing frequent and continuing support for behavior change, to reduce weight gain, and encourage weight loss and subsequently weight maintenance. NICE also recognizes the position of Commercial Weight Management Organizations (CWMOs) which follow guidance criteria for best practice. The UK cross-departmental government report ‘Healthy Weight, Healthy Lives’ acknowledged the important role of the commercial sector and other providers in “ensuring more people can access effective services in order to increase cost-effective provision of health service capacity” (48). An RCT involving 740 subjects compared a range of commercial primary care led 12-week weight reduction programs in those with obesity across a Primary Care Trust in Birmingham, England (49). Of the data available for 658 (88%) participants at the end of the programs, and 522 (70.5%) participants at one year, the results showed that all programs aided significant weight loss from baseline to the end of the program (between 1.37-4.43kg) and all achieved significant weight loss at one year (excluding general practice and pharmacy provision).

Following a feasibility study in 2006, one CWMO (Slimming World) has been operating in collaboration with Primary Care Trusts and National Health Service (NHS) Trusts, proposing a subsidized plan to provide free membership for 12 weeks to patients referred by their health care professionals. This project, involving 34,271 patients, was recently audited, and showed an average percentage weight change of -4.0% with a mean number of sessions attended of 8.9. For patients attending at least 10-12 sessions (n=19,907 or 58.1%), the mean percentage weight change was -5.5%. Weight gain was reduced in 92.1% of referred patients. The report concluded that referral to a CWMO is a feasible alternative for NHS weight management strategies, which accomplishes clinically effective weight loss (50). Slimming World makes provision for specific groups including those with T2D, cardiovascular disease and pregnancy, and often collaborates with health care professionals. In addition, whilst weight management and dietary choices are strongly emphasized, there is a graded approach regarding advice for physical activity. An online survey including 590 members attending Slimming World up to 2 years postpartum observed that “43% of respondents had reached their pre-pregnancy weight, whilst 41% indicated they now weighed less than before they were pregnant” (51). This data, although self-reported and in a possibly unrepresentative sample of responders, suggest that the program does help postpartum women to implement healthy lifestyle behaviors, lose weight and increase their self-esteem.

After consideration of the collated evidence and recommendations from governing bodies, a pragmatic pilot multicomponent randomized postpartum lifestyle modification program for overweight women with previous GDM (PAIGE) in combination with the CWMO Slimming World and the NHS was conducted between 2013-2014 (52). The results showed a significant weight reduction at 6 months among 31 women in PAIGE compared with the 29 women receiving routine care (means 3.9 *vs* 0.7 kg respectively; p=0.02) supporting its clinical utility. A larger, definitive trial was recommended to confirm the validity of the intervention. Importantly, the intervention would seek to investigate whether a lifestyle change program for overweight and obese women with previous GDM (delivered in combination with Slimming World and the NHS), could be effective in achieving weight loss, and in the longer term, potentially a reduction in the risk of T2D.

